### Measures

#### Assessment of inclusion/exclusion criteria

Telephone screeningDemographics, psychiatric screening (diagnostic expert system for psychiatric disorders – Stamm Screening Interview [56], International Diagnostic Checklists for ICD − 10 and DSM-IV [57]Study information and informed consentGeneral study information and informed consent, MRI information and informed consent, PET information and informed consent, genetics information and informed consent

#### Neuropsychological examination at baseline (NP I)

IntelligenceWortschatztest [58], Hamburg-Wechsler Intelligence Test for adults-revised – subtests: picture completion, similarities, block design, arithmetic [59]MemoryVerbaler Lern- und Merkfähigkeitstest [60], Wechsler-Memory Scale-revised – subtests: digit span, block span (forward and backward, respectively) [61], Cogpack – subtest: remembering [62]Executive functionLeistungsprüfsystem (comparable to the Raven Matrices): subtest 4 [63], Tower of London [64], Trail-Making Test B [65], Cogpack – subtest: reasoning [62].Stimulus interferenceComputerized version of the Stroop TestInformation processing speedTrail-Making Test A [65], Hamburg-Wechsler Intelligence Test for adults-revised: digit-symbol substitution test [59]Visual constructionRay-Osterrieth Complex Figure Test – copy [66].AttentionTest battery for attention performance – subtests: alertness, divided attention

#### Neuropsychological examination immediately after cognitive training (NP II)

In the second neuropsychological examination (NP II, post-training phase), the same test battery as in the baseline examination (NPI) will be applied. However, the tests measuring intelligence will only be applied once (at NP I). If available, we will apply parallel test versions to avoid retest effects.

#### Neuropsychological examination after 3 months (NP III)

In the third neuropsychological examination (NP III, follow-up), the same test battery as in NP II will be applied. If available, we will apply parallel test versions to avoid retest effects.

#### Neuropsychological training

Executive functions, memory, information processing speedCogpack: Cogpack is a computerized cognitive training and testing program. The subtests comparisons, searching, logic, anagrams, complete a logical block, and remembering will be appliedAlertnessAttention capacities will be trained using the test battery for attention performance, which permits us to assess/train a variety of attentional aspects. The subtests alertness and divided attention will be trained.Working memoryThe computerized training software TATOOL [67] will be used to apply a working memory training designed in accordance to Batian et al. [68]

#### Physical activity examination

ActigraphyObjective physical activity, sleep/wake and energy expenditure measurement solution. The portable wristband (GeneActive, Kimbolton, UK) uses a three-axis accelerometer, a heat flux sensor, a galvanic skin-response sensor, a skin-temperature sensor, and a near-body ambient temperature sensor to capture data for 1 weekGlobal Physical Activity QuestionaireThe Global Physical Activity Questionaire covers several components of physical activity typical of an elderly population. The score takes into account self-reported occupational, household and leisure activities items over a 1-week period (World Health Organization (WHO), http://www.who.int/chp/steps/GPAQ/en/)

#### Fitness examinations

Cardiovascular fitnessCardiovascular fitness will be assessed using a modified, graded, exercise-testing protocol in the field. Endurance capacity will be estimated on the basis of walking/running speed, the corresponding concentration of blood lactate and the perceived exertion of each participant.Additionally, the maximum oxygen uptake (VO_2_max) and the peak oxygen uptake (VO_2_peak) will be estimated using the 6-minute Walking Test.Motor fitnessGross motor fitness will be assessed using a test battery comprising the following basic motor skills:Static and dynamic balanceShort Physical Performance BatteryFeet tappingHand tappingKasten-Bumerang TestMovement-Coordination TestAgility TestFine motor fitness will be assessed using the following subtests of the Vienna Test System:Motor performance seriesSensomotor coodinationSpatial orientationReaction timeResponse inhibitionTime/movement anticipation

#### Imaging data acquisition

Structural MRIDTI, T1-weighted structural MRI, FLAIR, high-resolution T2-weighted structural MRIFunctional MRIResting-state MRI, task-related fMRI. For task-related fMRI, participants will perform three runs of the Hybrid Response Inhibition task [69]. Using identical visual stimulus material the Hybrid Response Inhibition task assesses three subcomponents of response inhibition: response interference, action withholding, and action cancelation (Fig. 3). Stimuli will be presented in the center of the screen. Participants will be asked to perform a button press according to the pointing direction of an arrow and to refrain from a button press whenever the ellipse surrounding the arrows turns blue (nogo−/stop trials). Event-related fMRI data acquisition will be performed using standard echo planar imaging sequences with whole-brain coverage and isotropic voxels. SPM 12 (http://www.fil.ion.ucl.ac.uk/spm) will be used to conduct all image preprocessing and statistical analyses. In addition to standard general linear model analyses, a BOLD lateralization index [70] will be computed for each subcomponent separately. The lateralization index is hypothesized to mediate transfer capabilities in older adults and to be associated with the structural integrity of the corpus callosum.PETThe amyloid tracer [18F]Florbetaben will be applied via a venous cannula. Subjects will be instructed to void their bladder to allow rapid excretion of unbound radioactivity. Subjects will be placed on the scanner approximately 70 min after injection. At 80 min p.i. (post injection) two low-dose computer tomography scans will be acquired for position and attenuation correction. At 90 mins p.i., the PET acquisition will be initiated. PET data will be acquired for 20 min. After the scan the subject will be asked about their well-being and instructed to void their bladder to accelerate excretion of radioactivity. Subjects will be instructed to minimize contact with small children and pregnant women for 12 h after tracer injection. The entire examination, including preparation and scanning procedures, can be finished within 3–3.5 h.

**Fig. 3 Fig3:**
[figure not shown]
The Hybrid Response Inhibition task. Participants are asked to press a button corresponding to the pointing direction of an arrow. Go trials consist of congruent trials; inhibition trials consist of incongruent trials (interference inhibition), occurrence of a no-go stimulus (blue ellipse; action withholding), or of a stop-signal (blue ellipse after a varying stop-signal delay; action cancelation)

#### Genetics

Two samples of 5 ml ethylenediamine tetraacetic acid blood will be collected from participants at the pre-training phase and at the post-training phase in Mainz and Rostock and at the pre-ACT-training phase, post-ACT-training phase, and post-cognitive-training phase in Cologne. Blood samples will be kept on ice for a maximum of 15 min and subsequently stored at − 80 °C in the recruiting centers. Frozen blood samples will be shipped on dry ice to the Laboratory of Molecular Genetics, Institute of Human Genetics, University Medical Center Mainz. There, deoxyribonucleic acid (DNA) extraction from one of the frozen blood samples taken at the pre-training phase will be performed on a chemagic Magnetic Separation Module I using the chemagic DNA Blood Kit special for the automated isolation of DNA from 5 ml whole blood followed by quantification of DNA on a NanoDrop 2000UV-Vis spectrophotometer. Genotyping for the single nucleotide polymorphisms rs7412 and rs429358 in the apolipoprotein E gene, rs5882 and rs1800775 in the *Cholesteryl Ester Transfer Protein* gene, rs6265 in the *BDNF* gene, rs2765 in the *Neurokinin.3 Receptor* gene, rs6439886 in the *Calsyntenin 2* gene, and rs17070145 in the *Kidney and Brain Expressed Protein* gene will be carried out from extracted genomic DNA samples using polymerase chain reaction followed by pyrosequencing on a Pyromark Q96 ID Instrument using PyroMark Gold Q96 SQA Reagents and the Pyromark Q96 ID software. The second blood sample taken at the pre-training phase and both blood samples taken at the post-training phase will be stored at − 80 °C for prospective analyses of training-induced epigenetic and transcriptome changes. Blood samples will be stored in secured rooms at the Institute of Human Genetics of the University Medical Center Mainz for a maximum of 60 years.

### Statistics

#### Sample size

Primary outcome: the analyses will focus on training gain transfer (defined as a binary criterion for each subject) and simultaneously incorporate measures of corpus callosum integrity and bihemispheric processing. The sample size calculation was performed based on main effects analyses where the effects of both measures will be considered as main effects. Assuming a transfer rate of cognitive training gains of about 15% for participants with low corpus callosum integrity, and a transfer odds ratio of 3 for participants with high corpus callosum integrity, a sample size of 160 provides a power of 0.8 at a significance level of 0.05 for a Wald Test in a logistic regression model. Assuming a dropout rate of about 15%, a total of 192 participants need to be included.

Secondary outcome: for evaluating physical training as a potential modulator of cognitive training gain transfer, ACT-induced fitness changes will be analyzed with respect to changes of corpus callosum integrity, as well as with respect to effects on transfer. The former analysis corresponds to considering the correlation between fitness changes and integrity changes. For the latter, an interaction between corpus callosum integrity and fitness changes with respect to transfer will be considered in a logistic regression model. Such an interaction can be expressed as a correlation between fitness changes and the degree of transfer in a group with low/high corpus callosum integrity. Based on the results by Voss et al. [14], we assume a correlation of about 0.43 between both measures. At a significance level of 0.05, 30 individuals per (equally sized) integrity group are needed to detect such a correlation with a power of 0.8. As a result, ACT needs to be performed for 60 individuals in total. Assuming a dropout rate of about 15%, 72 subjects at the German Sport University Cologne will undergo the extended experimental protocol.

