#### Secondary objectives

There is evidence that physical activity and cardiorespiratory fitness are associated with reduced brain tissue loss and reduced risk for cognitive impairment in aging humans [18, 19]. Moreover, aerobic exercise training increased gray and white matter volume in the prefrontal cortex [20] of older adults and led to significant improvements of executive function [21, 22]. Further, hippocampal and medial temporal lobe volumes were larger in older adults with greater cardiorespiratory fitness [19, 23], and larger hippocampal volumes mediated improvements in spatial memory [19]. Aerobic exercise training increases cerebral blood volume [24], perfusion [25] and the adult hippocampal volume. It has been suggested that the aforementioned structural changes are mediated by neurotrophins, in particular the brain derived neurotrophic factor (BDNF) [26]. We [27–30] and others [31, 32] demonstrated that exercise induces significant increases in levels of BDNF and other growth factors, and higher serum BDNF after aerobic training was associated with larger anterior hippocampal volume [33]. Using DTI, more recent studies measured brain structural integrity as a function of cardiorespiratory fitness and aerobic exercise training in HOA. Fractional anisotropy of the corpus callosum was reported to be positively correlated to cardiorespiratory fitness in HOA [34]. Thus, cardiorespiratory fitness might modulate age-related alterations of corpus callosum integrity. In addition, greater aerobic fitness derived from a walking program was associated with increases in white matter integrity of the frontal and temporal lobes, and improvement of memory performance [14]. Consistently, using resting state fMRI analyses, it has been shown that cardiorespiratory fitness is positively associated with functional connectivity in the Default Mode Network, and that this in part mediates improved performance on tasks requiring set-shifting, task switching, and spatial working memory [35]. Furthermore, 1 year of regular walking increased functional connectivity between parts of the frontal, posterior, and temporal cortices within the Default Mode Network and the Frontal Executive Network [35]. Of note, there is evidence that the beneficial effects of physical activity on cognitive performance is not limited to cardiorespiratory fitness but is also present after resistance [36–38] and coordination exercise training [39, 40]. Moreover, different types of physical training have been shown to affect different neurocognitive networks [40, 41]. We hypothesize that coordination exercise training positively modulates cognitive transfer abilities in HOA based on the following rationale: coordination training aims at improving the efficiency of complex body movements including eye-hand coordination, bimanual coordination, leg-arm coordination, and reactions to moving objects [40]. Such complex movements require bihemispheric interactions via the corpus callosum [42], and both, size and structural integrity of the corpus callosum typically change after sensorimotor skill acquisition [43]. These interactions are probably not limited to pure motor processes but rather include selective aspects of cognition necessary for adaptive motor behavior such as attention, inhibitory and facilitatory processes, working memory, and error-related processing. In line with this, it has been demonstrated that rather anterior corpus callosum projections to the prefrontal cortex than middle corpus callosum projections to the primary motor cortex predict bimanual motor learning [44].

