
In sum, aerobic exercise – and coordination exercise training are associated with positive structural and functional brain changes as well as improvements of cognitive performance in HOA. Moreover, cerebral regions targeted by these interventions are primarily involved in age-related cognitive decline including the corpus callosum, the hippocampus, frontal and temporal cortices, and the Default Mode Network. As a secondary outcome, we will determine if physical training, comprising aerobic and coordination components, modulates transfer of cognitive training gains in HOA. Moreover, we will determine the impact of baseline physical activity on transfer in HOA.

Subcortical cerebrovascular lesions reflected in white matter hyperintensities and cortical β-amyloid aggregation are highly prevalent and strongly age associated with central nevous system (CNS) pathologies [45]. Both findings are suspected to have a deleterious effect on neuronal function. White matter hyperintensities have been found to affect structural connectivity in the brain on the subcortical level [46]. Amyloid pathology, on the other hand, which is a hallmark of Alzheimer’s disease [47], has been discussed to affect regional synaptic function on the cortical level [48]. Although both findings have been associated with manifest cognitive decline or dementia, they are known to be present in a significant proportion of the cognitively healthy elderly, potentially leading to subclinical deficits [49, 50]. White matter hyperintensities frequently observed in the prefrontal cortex in clinically HOA have been linked to subclinical disturbances of executive function, whereas cortical amyloid deposition has been associated with a minor decline in memory function in this population [51]. Transfer capability represents a multidimensional cognitive function which requires executive and memory skills and presumably depends on highly efficient neuronal pathways including bihemispherical communication. Thus, the two mentioned pathologies are supposed to have a cumulative negative effect on transfer performance, even ahead of other cognitive symptoms. Consistently, as a further secondary outcome, the study aims at investigating white matter hyperintensities and cerebral amyloid burden as potential modulators of transfer of cognitive training gains in HOA.

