We and others found that Default Mode Network activity is related to cognitive function and cognitive reserve in HOA [52, 53]. Default Mode Network activation during cognitive tasks was accompanied by less default suppression with greater task demand and less connectivity among Default Mode Network regions as well as increased frontal activation [54]. Thus, since cognitive reserve capacity as referring to Default Mode Network might also predict transfer cabilities, resting-state fMRI connectivity measurements will be also conducted [55]. Moreover, based on the comprehensive data survey the study aims at modeling and analyzing multimodal, high-dimensional datasets with respect to transfer prediction and to build a robust individual index of transfer likelihood.

All secondary outcomes are summarized in Table 1.

**Table 1 Tab1:** Overview of secondary outcomes

Secondary objectives	To evaluate the predictive value of a preceding aerobic and coordination training for transfer of cognitive training gains in healthy older adults (HOA)
	To evaluate the predictive value of baseline physical activity on transfer in HOA. Baseline physical activity will be measured by a 1-week actigraphy and the Global Physical Activity Questionnaire (see “Measures” section below).
	To evaluate the predictive value of brain vascular lesion (as determined by T2-weighted magnetic resonance imaging (MRI), cortical amyloid burden (as determined by positron-emission tomography), higher default mode network activity (as determined by resting state functional MRI (fMRI) for transfer of cognitive training gains in HOA
	To model and analyze multimodal, high-dimensional datasets with respect to transfer prediction and to build a robust individual index of transfer likelihood

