### Population

#### Sample size

It is planned to include 237 cognitively healthy elderly subjects (aged 60 years and older) in total distributed over the three trial sites, satisfying the statistical power requirements for different research questions, as described below. Paticipants will be recruited by local newspaper announcements and flyers.

For the investigation of the primary objective, a sample size of 160 subjects has been determined based on a power calculation (see “Statistics”). Assuming a dropout rate of about 15%, the recruitment of subjects will be distributed as follows: Mainz: *N* = 60, Rostock: *N* = 60, German Sport University Cologne/University Hospital Cologne: *N* = 72.

For the investigation of the predictive value of a preceding ACT for the transfer of cognitive training gains in HOA (secondary objective), all 72 subjects recruited at the German Sport University Cologne/University Hospital Cologne (who are also part of the investigation of the primary outcome) will undergo an extended experimental protocol, including ACT followed by the cognitive training. The sample size of 72 subjects has been determined based on a power calculation (see “Statistics”). Since, so far, no evidence has been published showing that physical activity may have an impact on transfer via mechanisms other than brain structure and function, it is assumed that the preceding physical training in subjects recruited in Cologne will not confound the investigation of the primary objective.

To minimize/avoid bias, the following control subjects will be included: 15 HOA will be enrolled in Cologne undergoing the standard experimental protocol without ACT to assure that the net effect of the cognitive training does not differ from the effects at the other trial sites. To control performance alterations in the neuropsychological examinations for retest effects, an additional sample of 30 HOA, generated in Mainz (*N* = 10), Rostock (*N* = 10), and German Sport University Cologne/University Hospital Cologne (*N* = 10), will undergo the repeated neuropsychological examinations without cognitive training.

Within each trial site, participants will be distributed randomly to experimental or control groups, stratified centrally by the trial coordinator at the trial site University Medical Center Mainz. The study code is centrally managed by this trial site. Participants will be enrolled by their respective trial site.

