#### Analysis of secondary endpoints

For evaluating physical training as potential modulator of cognitive training gain transfer, correlations between fitness changes and integrity changes of the corpus callosum will be applied. Moreover, an interaction between corpus callosum integrity and fitness changes with respect to transfer will be considered in a logistic regression model. Such an interaction can be expressed as a correlation between fitness changes and the degree of transfer in a group with low/high corpus callosum integrity.

To evaluate the predictive value of brain vascular lesion, cortical amyloid load, higher Default Mode Network activity, and genetics for transfer of cognitive training gains in HOA, a logistic regression model with transfer as the dependent variable is used. All effects of the potential predictors are included as main effects. Additionally, to adjust for ACT, ACT and all interactions with ACT are included in the model as independent covariates.

To determine the impact of ACT on the structural integrity of the corpus callosum, Default Mode Network activity, BDNF, motor fitness, and VO_2_peak/VO_2_max, logistic regression models for these variables are fitted. ACT will be included as an independent variable. Additionally, the model will be adjusted for all other variables and the interactions with ACT. For example, the model for structural integrity of the corpus callosum will include ACT, Default Mode Network activity, BDNF, motor fitness, VO_2_peak/VO_2_max and all interactions with ACT as independent covariates.

Similar models will be fitted to examine the association between baseline physical activity and the structural integrity of the corpus callosum, Default Mode Network activity, and BDNF. Here, baseline physical activity and all possible interactions with baseline physical activity will be additionally included as independent covariates.

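### The test named for fitness change and transfer is an integrity-by-fitness interaction, sized as if it were a within-group correlation; no stated analysis tests the overall association

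*Protocol article*

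**What the plan says.** **The question.** The Secondary objectives section of the protocol article states: "We hypothesize that coordination exercise training positively modulates cognitive transfer abilities in HOA". It adds that, as a secondary outcome, "we will determine if physical training, comprising aerobic and coordination components, modulates transfer of cognitive training gains in HOA". Table 1 lists the predictive value of preceding combined aerobic and coordination training (ACT) for transfer. None of these is conditional on callosal integrity.

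**The analysis.** Under Statistics, Sample size, the secondary-outcome paragraph promises two analyses of fitness change: one against change in callosal integrity, one for effects on transfer. The first is a correlation. The second reads: "For the latter, an interaction between corpus callosum integrity and fitness changes with respect to transfer will be considered in a logistic regression model". The text then says that such an interaction "can be expressed as a correlation between fitness changes and the degree of transfer in a group with low/high corpus callosum integrity". It assumes a correlation of about 0.43 and derives 30 subjects per integrity group for power 0.8 at level 0.05, hence 60 in total and 72 after dropout.

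Analysis of secondary endpoints repeats the specification, "Moreover, an interaction between corpus callosum integrity and fitness changes with respect to transfer will be considered in a logistic regression model", and the same gloss.

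**Related models.** The model for vascular lesions, amyloid, Default Mode Network activity and genetics includes ACT and its interactions, for adjustment. The primary analysis relates callosal integrity and bihemispheric processing to transfer, adjusted for age; fitness change is not in it.

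**The concern.** Write the logistic model as logit P(transfer) = b0 + b1·integrity + b2·fitness change + b3·(integrity × fitness change). The interaction test is of b3 = 0, that is, the same fitness slope at low and high integrity. The objective concerns whether fitness gains go with more transfer at all. If they help both integrity groups equally, b3 is zero and the objective's hypothesis is true. Conversely, b3 can be non-zero when the average benefit is nil, because the slopes are opposite.

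A correlation within one group is a third quantity: it asks whether the slope in that group is zero. The protocol treats it as the interaction, and takes the sample size from one test and the model from the other.

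At stake is the interpretation of a 20-week training component in 72 people. An analyst who fits the named term would usually obtain a non-significant result even when fitness gains help everyone.

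**Working it through.** **1. The protocol's own figure.** Inputs: r = 0.43, level 0.05, power 0.8 (Statistics, Sample size). Sidedness is not stated. For one correlation against zero with Fisher's z, n = ((z_alpha + z_power)/atanh r)² + 3, and atanh(0.43) = 0.460.
- One-sided: ((1.645 + 0.842)/0.460)² + 3 ≈ 32.2, so 33; power at n = 30 is 0.77.
- Two-sided: ((1.960 + 0.842)/0.460)² + 3 ≈ 40.1, so 41; power at n = 30 is 0.67.
- The t-test of the correlation at n = 30 gives one-sided power 0.79 (bivariate normal) or 0.82 (fixed x), and two-sided power 0.68 or 0.71.

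So 30 per group is reproduced, approximately, as the one-sided size for a correlation inside a single group. Dropout: 60/0.85 = 70.6, against 72 stated.

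**2. The same 30 per group, used for a difference between groups.** The standard error of a difference of two Fisher z values is √(2/27) = 0.272.
- 0.43 in both groups, which is the sizing assumption: the difference is 0 and the rejection rate is 5%.
- 0.43 against 0: 0.460/0.272 = 1.69, so two-sided power is Φ(1.69 − 1.96) = 0.39 (one-sided 0.52). For 80% two-sided, n = 2·(2.802/0.460)² + 3 ≈ 77.2, so 78 per group.

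**3. The logistic interaction under an equal benefit.** Model: logit P = logit(0.15) + ln 3·High + ln(OR)·F, with F standard normal and half the subjects in each integrity group. The 15% and the odds ratio of 3 are the protocol's primary-outcome assumptions. The odds ratio per SD of fitness change is an assumption, shown as a range. There were 3000 runs per setting, two-sided 0.05.

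| OR per SD | N | Interaction, Wald | Interaction, LR | Main effect given integrity, LR |
|---|---|---|---|---|
| 1.5 | 60 | 3.8% | 7.3% | 27.9% |
| 1.5 | 72 | 4.4% | 7.1% | 30.9% |
| 2.0 | 60 | 2.6% | 6.7% | 59.2% |
| 2.0 | 72 | 3.7% | 6.0% | 65.9% |
| 2.8 | 60 | 2.6% | 6.9% | 88.4% |
| 2.8 | 72 | 2.7% | 6.5% | 93.8% |

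The Monte Carlo standard error near 28% is √(0.28·0.72/3000) = 0.8 points, so a repeat run can differ by up to about two points. At an odds ratio of 4 the Wald interaction falls to 1.4–1.6%.

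**4. Effect wholly through the callosum.** Fitness change and integrity change are correlated 0.43, and transfer depends only on post-training integrity. Assumptions not in the document: 25% mean transfer, and a log odds ratio for integrity of 1.1–2.0 per SD. The interaction rejects in 2.6–4.5% (Wald) or 4.8–7.0% (likelihood ratio). The unadjusted fitness effect is detected in about 15–34%. Adjusted for pre-training integrity it is 18–40%; adjusted for post-training integrity, only 5–9%.

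**The case against.** **The gloss may be the intended test.** If so, a uniform correlation of 0.43 is detected in each group with power of about 0.67–0.71 two-sided or 0.77–0.82 one-sided. A reader might infer that the ACT component has only about a 2–8% chance of finding a uniform benefit, whatever is done. The document does not support that: the figure belongs to the interaction alone. The objection limits the size of the point but does not remove it, because both sections name the logistic interaction and the gloss is not equivalent to it.

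**The callosal route is not ignored.** A reader might infer that the plan misses it. In fact the fitness-change/integrity-change correlation covers the first leg, and the primary analysis covers the second. This stands, but the legs are planned separately and neither relates fitness change to transfer. Nor is it shown that mediation satisfies the interaction null exactly; the simulation shows only rejection near the nominal level.

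**ACT appears in another transfer model.** It does, as an adjustment term alongside all its interactions. That is not a stated test of fitness change.

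**The conclusion of no modulation is nowhere written.** Correct. A reader might infer that a non-significant interaction would be reported that way, but modulation is evaluated by two analyses, and a positive fitness-integrity correlation would also count.

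**The details may sit in an analysis plan.** An interaction model normally contains the fitness main effect, and a plan could test it. But the protocol has already named the term and sized the study, so this is a matter of what it states.

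**The interaction has a use.** With an odds ratio of 2.8 in the low-integrity group only and N = 60, its likelihood-ratio test has 36% power, against 25% for the main effect. This is a reason to keep it as a secondary question.

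**Conclusion.** The point holds in a limited form. Both statistical sections equate two different tests. The one actually specified for effects on transfer asks whether the fitness slope differs by integrity, whereas the objective asks about an overall effect. Under an equal benefit, including the sizing assumption of 0.43 in each group, the interaction rejects at about its nominal level (roughly 2–8% at N = 60–72). The fitness main effect given integrity would have about 28–31%, 59–66% and 88–94% power at odds ratios of 1.5, 2 and 2.8 per SD. Those odds ratios are assumptions, but the contrast holds at each of them. No stated analysis tests the overall association of fitness change with transfer.

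It would go too far to say that the ACT component cannot inform its hypothesis: the fitness-integrity correlation and the within-group reading both bear on it. This is a secondary objective, and a correction that should be made before analysis.

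**What to change.** In Statistics, Sample size (secondary outcome) and in Analysis of secondary endpoints:

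- Make the test of effects on transfer the main effect of fitness change over all ACT subjects, in a logistic regression without the interaction term, adjusted for pre-ACT callosal integrity and age. Do not adjust for post-ACT integrity, which would remove a mediated effect.
- Keep the integrity × fitness-change interaction as an exploratory question, and state that a non-significant interaction is not evidence against modulation of transfer.
- Delete the sentence equating the interaction with a within-group correlation.
- Optionally, report the two pathway legs already planned as a joint-significance test. With integrity change assumed to be half the variance of post-ACT integrity, its power is about 0.94 × 0.43 = 0.40 using 60 ACT subjects only, or 0.94 × 0.84 = 0.79 if the integrity-transfer leg uses all 160.

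The cost is wording and one or two models on data already to be collected. There are three downsides. The interaction becomes exploratory. The association within ACT subjects is predictive, not causal, and does not contrast ACT with no ACT. If the effect runs wholly through the callosum, the fitness effect has only about 15–34% power (18–40% with the pre-ACT adjustment).
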